### Secondary research hypotheses

1. There is a beneficial effect of pressure sensors upon health outcomes (transfer and mobility, fear of falling, quality of life, length of hospital stay and residential status on discharge) in hospitalised older people.

2. That the intervention above is cost-effective compared to usual care from a secondary care NHS perspective.

3. That there are groups of patients in whom the health or economic benefits from the intervention are greatest.

4. That the sensor system is acceptable to staff and patients and practical for use in an acute hospital setting.

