### Sample size

Based on data obtained from our wards during 2005, we anticipate a rate of bedside falls of 8.0 per 1,000 bed days in the control group, assuming that 53% of all falls occur at the bedside and that the average length of stay is 19 days (mean number of falls per patient = 0.15). To detect a 35% reduction in the rate of bedside falls among the intervention group, assuming 80% power, alpha = 0.05 and an over dispersion parameter of 1.5 (to allow for non-independence of falls within individuals), 905 participants are required in each arm of the trial.

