### Analysis

#### Quantitative analysis

Analyses will be undertaken on an intention to treat. Intention to treat analysis is defined in this study as an a priori plan to analyse the data according to the groups to which the subjects were randomised regardless of the treatment they received.

Fall rates for each group will be expressed as number of bedside falls per 1,000 bed days. The number of bedside falls per patient will be compared between groups using Poisson regression allowing for over dispersion, with length of stay in days as an offset. Crude models containing intervention group only will be fitted initially, whilst additional models will adjust for the effects of age, MMSE and mobility/transfer scores. Interactions between each of these three variables and treatment group with respect to our primary and secondary outcome measures will also be examined, with covariates dichotomised where necessary. For other secondary outcome measures, groups will be compared using the independent samples t-test for continuous outcomes (or Mann-Whitney U test if assumptions for using the t-test are not satisfied following appropriate transformations of the data) and the chi-square test for binary/categorical outcomes. The rate of falls in the trial wards in the 12 months prior to the trial commencing will be compared with the rate of falls in the control arm during the trial using Poisson regression, allowing for overdispersion as appropriate. A significance level of p < 0.05 will be used for all analyses.

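### The protocol permits age, MMSE and mobility/transfer scores to be dichotomised in the interaction tests, although the tests do not need a split and a split would cost information

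*Protocol article*

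**What the plan says.** Secondary hypothesis 3 in the Protocol article (Secondary research hypotheses) is "That there are groups of patients in whom the health or economic benefits from the intervention are greatest". The Quantitative analysis section serves it with treatment-by-covariate interactions for age, MMSE and mobility/transfer scores, on the primary and secondary outcomes, "with covariates dichotomised where necessary". The article does not say what would make a split necessary, and does not say that a split would be accompanied by a test on the unsplit covariate.

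The MMSE is collected as a 30-point score and mobility/transfer through the Barthel index (Table 1 and the baseline data section). Age is numeric. Fall rates are to be analysed by Poisson regression allowing for overdispersion, with adjusted models containing the same three covariates. For the other secondary outcomes the article names the t-test, the Mann-Whitney test and the chi-square test.

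**The concern.** A Poisson model accepts the product of treatment group and a numeric covariate directly. The simple two-group tests named for the other secondary outcomes cannot test an interaction at all, whether or not the covariate is split, so those outcomes need a regression in either case. Splitting therefore solves no problem in the test. It replaces the recorded score with a two-level version and treats everyone on one side of the cut as alike.

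What is at stake is hypothesis 3. The trial is sized for the main effect, and interactions are estimated much less precisely (step 2 of the working), so there is little information to give away. A result that depends on where a score was cut is also harder to interpret than a trend across the score.

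**Working it through.** **Inputs from the Protocol article, Sample size:** control rate 8.0 bedside falls per 1,000 bed days; mean stay 19 days; rate ratio 0.65 (a 35% reduction); power 80%; alpha 0.05, taken as two-sided; overdispersion 1.5; stated size 905 per arm. **Assumed, because the article does not give them:** the covariate distributions and the shape of the true interaction.

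**1. The plan's own figure.** Mean control falls per patient: 8.0 × 19 / 1,000 = 0.152. A Poisson regression formula with the null variance at the control rate gives the total:

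N = 1.5 × [1.96 × √4 + 0.842 × √(2 + 2/0.65)]² / (0.152 × (ln 0.65)²) ≈ 1,799

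That is 899.5 per arm, or 911.5 per arm with the rounded mean of 0.15. Both are within 1% of the stated 905. The figure concerns the main effect. The article states none for interactions.

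**2. Precision of an interaction at this size.** Expected falls: 905 × 0.152 = 137.6 (control) and 137.6 × 0.65 = 89.4 (sensor). If a split divides the falls evenly, each half has 68.8 and 44.7.

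SE of the log ratio of rate ratios = √[1.5 × (2/68.8 + 2/44.7)] = 0.33

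For 80% power the log ratio must be (1.96 + 0.842) × 0.33 ≈ 0.93, a ratio of rate ratios of about 2.5 (or 0.39). Only large interactions are detectable.

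**3. Information kept after one split, linear interaction.** This is the squared correlation between the covariate and its split version, with a proportion p on one side of the cut.

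- Normal covariate: φ(c)² / [p(1−p)]. At the median, 0.3989² / 0.25 = 0.637.
- Uniform covariate: [p(1−p)/2]² / [p(1−p)/12] = 3p(1−p). At the median, 0.75.
- Skewed bounded scores (beta 2,1; 3,1.5; 5,2) and a U-shaped score (beta 0.5,0.5): by simulation.

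| Information lost | 50/50 | 30/70 | 20/80 |
|---|---|---|---|
| Normal | 36% | 42% | 51% |
| Uniform | 25% | 37% | 52% |
| Skewed bounded | 31–35% | 30–50% | 39–64% |
| U-shaped | 19% | 37% | 56% |

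With 1,810 patients and a median split, the interaction information is that of about 1,810 × 0.637 = 1,152 patients (normal) or 1,810 × 0.75 ≈ 1,358 (uniform).

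**4. Effect on power.** Power after the split = Φ[(z + 1.96) × √(information kept) − 1.96], where z is the normal quantile of the power before the split. The starting powers are illustrations and do not come from the article.

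- From 80%, normal covariate: 61% at 50/50, 57% at 30/70, 50% at 20/80. Uniform at 50/50: 68%.
- From 50%, normal covariate: 35%, 32% and 28% at the same three cuts.

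**5. Check in an overdispersed count model.** Simulating 1,810 patients with a strong linear interaction and a median split, power fell from 94% to 80% (normal) and from 94% to 86% (uniform). The squared ratio of mean test statistics was 0.57 and 0.72, somewhat below the 0.637 and 0.75 of step 3 and in the same direction.

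**The case against.** The article does not commit to dichotomising. The adjusted models in the preceding sentence name the same covariates with no mention of categories, so keeping them continuous is a natural default, and a covariate left unsplit loses nothing. This stands: the loss is conditional.

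A reader might infer that the plan throws away a third or more of the information about who benefits. The article does not support that. It permits a split without requiring one, it gives no distributions, and at a median split the loss ranges from 19% to 36% across the shapes tried. The straight-line interaction is also an assumption. If benefit changes in a step near the cut, the split loses little or nothing, and the linear term may be the less efficient choice.

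A reader might also infer that the lack of cut-points shows they would be picked after seeing the data. That does not follow either. An article commonly leaves cut-points to a statistical analysis plan, which may exist and is not shown. Their absence is not the point here. Fixing them would curb data-driven choice but would not restore information lost by splitting.

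Finally, regression is named only for fall rates, so the other secondary outcomes have no stated interaction model, and hypothesis 3 speaks of groups of patients. Both are correct. The first means the fix must ask for a regression there. The second gives grouped estimates a place in presentation, but it does not make a split necessary for the test.

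**Conclusion.** The point holds as a free improvement to a secondary analysis. The protocol leaves open a form of the interaction test that the recorded data do not call for. If that form is used and the true interaction is linear, the cost at a median split is about a third of the information for a roughly normal covariate and about a quarter for a flat one. It is usually more at unequal cuts, and less under a threshold effect near the cut. Which case applies to age, MMSE or mobility/transfer cannot be settled from the article. The primary comparison and the 905 per arm are untouched.

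**What to change.** Delete "with covariates dichotomised where necessary" from the description of the tests. State that each treatment-by-covariate interaction will be tested with age, MMSE and mobility/transfer score kept in score form: a linear term, with a check for non-linearity such as a spline. Use the planned Poisson model for fall rates and a regression suited to the outcome type for the other secondary outcomes. Use pre-specified cut-points only to display effects by group. The cost is a sentence or two of analysis wording; no new data are needed.

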### Outcome measures

#### Definition of primary and secondary outcome measures

The primary outcome measure is the number of bedside in-patient falls per 1,000 bed days from time of randomisation until the participant is discharged from the ward.

A bedside fall is defined as an unexpected event in which the participant comes to rest on the ground, floor or lower level in the area around the bedside, with the bedside being defined as the area encompassed by the curtained area surrounding the bed. For participants in side rooms, the bedside is defined as the area of the room.

The secondary outcome measures are:

a. Number of injurious in-patient falls per 1,000 bed days, defined as falls resulting in abrasion, bruise, swelling, cut, laceration, dislocation, fracture or muscle sprain or strain.

b. Length of hospital stay.

c. Residential status on discharge.

d. Transfer/mobility score and activities of daily living, measured using the Barthel Index [26].

e. Fear of falling, measured using the Modified Falls Efficacy Scale (mFES) [27] to ascertain any differential fear of falling in the two participant groups due to an increased awareness of a potential for a fall, or a greater sense of safety arising from sensor use.

f. Health related quality of life, measured using the EUROQOL EQ-5D [28].

g. Participant and staff experience of using bed and chair sensors. This sub-study will be reported separately.

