##### (a) baseline data

The baseline data collected at recruitment originates from face to face interview between researcher and patient, the patient's medical and nursing notes, and/or carer.

Baseline data includes:

a. Demographic and residential details, reason for admission, time since admission.

b. Any previous history of falls, and any resulting fractures.

c. Mobility and transfer before the illness that precipitated admission, and at the time of recruitment (measured by the Barthel ADL index).

d. 30 point Mini Mental Stare examination (MMSE).

e. Health related quality of life measured using the EuroQol EQ-5D.

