##### (b) follow up data

Follow up data are collected one day prior or on the day of discharge.

Follow up data includes:

a. Falls, ascertained from hospital incident reporting forms. The use of these incident forms in NUH to record falls is mandatory and enforced by clinical governance processes. Members of the research team collect copies of hospital incident reporting forms from participating wards. Data such as fall event, time, and place, injuries sustained and subsequent actions taken are recorded. Where a medical opinion has been requested, the outcome is recorded, together with any investigations requested. In addition, aggregated, anonymzed data on falls will be collected from hospital incident reporting forms for the trial wards for the 12 month period prior to the trial commencing. The rate of falls in the period prior to the trial commencing will be compared with the control arm rate of falls during the trial to explore whether the use of sensors increases the rate of falls in the control arm.

b. Transfer/mobility and activities of daily living (Barthel ADL). This information is ascertained from the participant or carer, and/or their medical and nursing notes.

c. Quality of life (EuroQol EQ-5D) ascertained by participant interview. Where a participant is unable to participate in an interview, health related quality of life is ascertained from the carer and named nurse.

d. Fear of falling (mFES), ascertained by participant interview. Where a participant is unable to take part in an interview due to poor cognitive ability, this assessment is coded appropriately and excluded from analysis.

e. Mini Mental State Examination (MMSE), through participant interview. The baseline assessment does not account for any acute delirium secondary to the patient's condition on hospitalization, which may improve with treatment. The change in delirium may have an effect on the risk of falling.

f. Length of stay and residential status on discharge, ascertained from medical records.

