Data on resource use will be collected for the economic analysis and will include the costs of investigations and interventions arising from any fall whilst in hospital and the length of stay. These data will be obtained from the medical records. Unit costs will be derived from published sources. The cost of the intervention will include rental costs, plus costs of any sensor failures and cost of installing, cleaning, and responding to sensor alarms. Nursing staff on each ward will be asked to record sensor problems and reasons for sensor removal.

Nurse time taken to respond to sensor alarms will be ascertained from an observational study to measure the content and process fidelity of the intervention. The researchers fitting the bed sensors record the length of time taken to fit sensors.

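### Length of hospital stay has no stated start point and is compared unadjusted, although time since admission is recorded at baseline; on its ordinary reading the test may lose some power

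*Protocol article*

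**What the plan says.** All places are in the protocol article.

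- **Definition of primary and secondary outcome measures.** The falls outcome has an explicit window, "from time of randomisation until the participant is discharged from the ward". The second secondary outcome is given only as "b. Length of hospital stay".
- **(b) follow up data.** The source is stated, but the start date is not: "Length of stay and residential status on discharge, ascertained from medical records". The resource-use text closing that section also counts stay as a cost item: "the costs of investigations and interventions arising from any fall whilst in hospital and the length of stay".
- **(a) baseline data.** The items collected at recruitment include "Demographic and residential details, reason for admission, time since admission".
- **Quantitative analysis.** The main rule reads "For other secondary outcome measures, groups will be compared using the independent samples t-test for continuous outcomes". A rank test is allowed as the fallback, in these terms: "or Mann-Whitney U test if assumptions for using the t-test are not satisfied following appropriate transformations of the data". The adjusted models are described by "additional models will adjust for the effects of age, MMSE and mobility/transfer scores"; time since admission is not among these covariates.
- **Health economic analysis.** Differing lengths of stay are named as a source of cost difference, and costs and benefits are limited to the period of the study.

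**The concern.** Patients are recruited after admission, so part of a stay counted from admission is already fixed when the patient is randomised. Those days cannot respond to the sensors. They enter both arms alike, so randomisation protects the comparison, but they can contribute variation unrelated to treatment. If stay is analysed after log transformation or by ranks, they also make a given cut in remaining stay look smaller in relative terms.

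The trial records the quantity that would remove this variation and then does not use it. At stake is the chance of detecting a shorter stay, which is part of the first secondary hypothesis, and possibly the precision of the bed-day component of incremental cost.

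**Working it through.** **The plan's own figure.** The only sample size given is for bedside falls, 905 per arm. The Signorini formula for overdispersed Poisson regression reproduces it. With overdispersion 1.5, rate ratio 0.65 and mean falls 0.15:

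N per arm = ½ × 1.5 × (1.960×√4 + 0.842×√(2 + 2/0.65))² / (0.15 × (ln 0.65)²) ≈ 911.

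With the unrounded mean 8.0 × 19 / 1000 = 0.152 it gives 899, and with 0.151 it gives 905. The plan states no power for length of stay, so everything below uses 905 per arm with assumed inputs and a two-sided 5% level.

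**Raw days.** Let *pre* be days before and *post* days after randomisation. Allocation cannot change *pre*, so the expected difference in total days equals the expected difference in *post*. Only the variance changes:

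SD_total = √(SD_post² + SD_pre² + 2ρ·SD_pre·SD_post).

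Assume SD_post = 19 days and a difference that gives 80% power on *post* alone: (1.960 + 0.842) × 19 × √(2/905) = 2.50 days. Power on total stay is Φ(2.50 / (SD_total·√(2/905)) − 1.960):

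| SD_pre (days) | ρ = 0 | ρ = 0.2 |
|---|---|---|
| 2 | 79.6% | 77.9% |
| 3 | 79.0% | 76.6% |
| 5 | 77.3% | 73.4% |
| 10 | 69.8% | 63.2% |

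For SD_pre = 3 and ρ = 0, for example, SD_total = √(361 + 9) = 19.24. With ρ = −0.2 and SD_pre from 1 to 7 days, power is 80.5% to 81.5%, so nothing is lost.

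**Log and rank scales.** Stay is usually skewed, so the plan's transformation or Mann-Whitney route is plausible. Assume a mean total stay of 19 days (Sample size section), exponential delay independent of remaining stay, lognormal remaining stay with coefficient of variation (CV) 0.8 or 1.0, and a true 10% cut in remaining stay. Power was obtained by simulating large arms and converting the standardised difference to 905 per arm. Log-scale t-test, total stay versus stay from randomisation:

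| Mean delay | CV 0.8 | CV 1.0 |
|---|---|---|
| 2 days | 87% vs 89% | 74% vs 77% |
| 4 days | 81% vs 89% | 67% vs 77% |
| 6 days | 71% vs 89% | 58% vs 77% |

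- Mann-Whitney is similar: at 4 days, 79% vs 88% and 65% vs 74%.
- If delays vary less (gamma, shape 4), the log-scale loss is about 1 point at 2 days, 3 to 4 at 4 days and 7 to 9 at 6 days.
- On raw days with exponential delay it is 1 point or less, 3 to 5, and 9 to 13.

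**Correlation between delay and remaining stay.** At a 4-day mean exponential delay, ρ = +0.2 raises the log-scale loss to 12 to 14 points. ρ = −0.2 lowers it to 4 to 5 points (86% vs 90%, 73% vs 78%). In a separate simulation (remaining stay with mean and SD 16 days, 12% reduction, 1,000 runs), a 2-day delay with ρ = 0.3 lost about 5 points on the log and rank scales (85.0% vs 90.0%; 83.7% vs 88.6%).

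**Relative effect.** With 4 of 19 days elapsed, a 10% cut in the remaining 15 days is 1.5 days, or 10% × 15/19 = 7.9% of total stay.

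**Adjusting instead.** Putting time since admission into the model for total stay did not lower power beyond simulation error at any correlation from −0.2 to 0.2. At zero correlation it gained about 0 to 2 points at mean delays of 1 to 2 days, 3 to 7 at 4 days and 9 to 14 at 6 days.

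**The case against.** The strongest reply is that nothing in the article says the earlier days are included. The Quantitative analysis section uses length of stay in days as the offset for falls counted from randomisation, which suggests that there the term means time from randomisation. Recording time since admission is also what a team would do if it meant to compute stay from randomisation. This stands: inclusion is the ordinary reading and not a stated rule, and the term is ambiguous.

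A reader might infer that the treatment effect is diluted. In days it is not. Shrinkage arises only on a log or rank scale or when the effect is quoted as a percentage, and 10% of 15 days and 7.9% of 19 days are each correct for their own quantity.

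A reader might also infer that these days certainly enter the cost comparison. The Health economic analysis section limits costs to the period of the study, which fits a count from trial entry at least as well. Mean incremental cost would in any case be unbiased.

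Finally, total stay is a conventional outcome, an unadjusted test of it is valid, and an analysis plan may settle the start date. That removes any charge of error. It does not remove the point, because the article itself names the tests and lists covariates that leave out a relevant item already collected.

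**Conclusion.** The point holds as a minor matter of definition and efficiency. The start of length of stay should be stated, and the recorded time since admission should be used. Validity is not in question.

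The documents do not support a flat statement that the test loses power: they give no recruitment delay, no spread of stay and no correlation, and no power is claimed for this outcome. With delay independent of remaining stay, the loss is about 0 to 3 points at a mean delay of 2 days or less. It exceeds 5 points on the log or rank scale only when delays average about 4 days or more and vary. A positive correlation brings that threshold down; a negative one reduces the loss and on raw days can remove it.

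**What to change.** Add one sentence to the outcome definition or the analysis plan, choosing one of two forms:

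1. Compare total stay in a linear model on the chosen scale, with time since admission as a covariate. This is the safer form. With ρ = −0.2 and SD_pre = 3 in the raw-days calculation, total stay has 81.5% power, stay from randomisation 80%, and the adjusted model (residual SD 19 × √(1 − 0.2²) = 18.6) 81.6%.
2. Define the outcome as days from randomisation to hospital discharge, that is, recorded total stay minus time since admission. This also serves if the Mann-Whitney test is used, since that test takes no covariate.

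Report total stay from admission descriptively. State that costed bed days use the same start point, consistent with the study-period limit in the Health economic analysis section.

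The change needs no new data and no more patients. Its small downside, under the second form, is that the headline figure is no longer the conventional total stay.

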#### Health economic analysis

A cost-effectiveness and cost-utility analysis will be performed using established methods [29]. The comparative analysis will be undertaken from a secondary care NHS perspective capturing direct secondary care health service costs and benefits over the study period. In addition to measuring the cost of the intervention, the resources consumed in the two arms of the study are likely to differ as there is the potential for differential rates of investigations and treatments, and differential lengths of stay in hospital. Resources will be valued using published unit cost data or where needed using locally derived unit costs. In this study we will use falls prevented as the effectiveness measure and change in utility as measured using the EuroQol EQ-5D as baseline and discharge [30].

An incremental economic evaluation comparing the sensor group to the standard care will be undertaken to estimate mean incremental cost-effectiveness. If one group is clearly dominant (less costly and more effective) a recommendation will be made. If non-dominance occurs (that is if costs are greater and the intervention is more effective or if the intervention is cheaper and less effective), an incremental cost-effectiveness ratio will be produced.

Probabilistic sensitivity analysis will be undertaken to test the robustness of the results. The confidence region around the incremental cost effectiveness ratio will be estimated using appropriate statistical techniques such as the non-parametric bootstrap method. This stochastic analysis will enable cost effectiveness acceptability curves and a cost effectiveness acceptability froniter to be produced [31] illustrating the uncertainty surrounding the optimal decision. Estimates of the incremental cost, incremental cost effectiveness and the uncertainty around these estimates will enable us to examine the implications of rolling out sensors nationally.

